**Figure 6 Figure 7**

***Blood collection and analyses***

Blood samples collected will be sent to commercial pathology laboratories for pathological profiling which includes red blood cell count, white blood cell counts and platelets count. Serum samples will be analyzed for the interleukins such as interleukin TNF- α , IL-1β, and IL-6 by commercial enzyme-linked immunoabsorbent assay (ELISA) kit following manufacturer’s instructions. Samples may need to be diluted with appropriate amounts of buffer provided in the kit to give constant dilutions prior to analyses. A standard curve will be constructed, and the concentration of samples will be read against the standard curve and expressed as concentration per unit of the samples. The modulation of these immunological parameters will also be determined using gene expression analyses using via real-time PCR.

**Operational definition**

(1) Alcohol dependence: a chronic disease in which a person craves drinks that contain alcohol and is unable to control his or her drinking.

(2) Alcohol withdrawal: a set of symptoms that can occur following a reduction in alcohol use after a period of excessive use. Symptoms typically include anxiety, shakiness, sweating, vomiting, fast heart rate, and a mild fever. More severe symptoms may include seizures, hallucinations, and delirium tremens. Symptoms typically begin around six hours following the last drink, are worst at 24 to 72 hours, and improve by seven days.

(3) Probiotics: Probiotics are live microorganisms promoted with claims that they provide health benefits when consumed, generally by improving or restoring the gut flora.

(4) Acceptance and commitment therapy: a third-generation cognitive behavioral approach which uses acceptance and mindfulness processes, and commitment and behavior change processes to produce psychological flexibility. The latter is defined as the ability to contact the present moment more fully as a conscious human being and to change or persist in behavior when doing so serves valued ends.

(5) Alcohol craving: an intense, urgent, or abnormal desire or longing to consume alcohol.

**Study flowchart**

**Figure 3.1. Flow chart of the study**

**Data analysis**

All data analysis will be performed using SPSS software version 25.0 (SPSS Inc, Chicago, IL, USA). Descriptive statistics for socio-demographic and clinical characteristics, CIWA-Ar, PACS, AUDIT, VAS, HAMD, and HAMA scores, ERP analysis, and serum pro-inflammatory cytokine levels will be computed. All categorical variables will be presented in frequency and percentage, while all continuous variables will be reported in mean and standard deviation or median and interquartile range, depends on normality. Differences in socio-demographic and clinical characteristics between the three groups will be computed with Pearson’s chi square test or one way ANOVA or Kruskal Wallis test.

The mean difference in the primary outcome (CIWA-Ar, PACS, AUDIT, and VAS scores) for the three randomized groups (ACT, probiotic, and palcebo groups) at each specific time point (pre-intervention, 2 weeks at completion of conventional treatment [t0], post-treatment at 8 weeks [t1], post-treatment at 12 weeks [t2], and post-treatment at 24 weeks [t3]) will be assessed using one way analysis of variance (ANOVA) followed by false discovery rate adjustment. For the main pool analysis, mixed ANOVA is used to determine the interaction between the groups (ACT, probiotic, and placebo groups) and time points (t0, t1, t2, and t3) on the primary outcome ( CIWA-Ar, PACS, AUDIT, and VAS scores; interaction = intervention × time; where time is a within-subject variable and intervention effect is a between-subject variable). The main effects of intervention in the groups and time points will be presented as estimated marginal mean and standard error of mean. The study’s primary analysis will follow the intention-to-treat (ITT) principle. The data analysis for the study’s secondary outcomes (severity of anxiety and depressive symptoms, pro-inflammatory cytokines, EEG characteristics, and fecal microbiota) will be conducted similarly to the primary outcomes’ calculation. Statistical significance will be two-tailed and set to p < 0.05.

To handle any missing data, if the missing data represent less than 5% of the study’s total collected data, they will be ignored. If the missing data represent more than 5% but less than 40% of the total collected and are assumed to be randomly missing, then multiple imputation (restricted maximum likelihood estimation) will be performed using Stata 15. However, if the missing data represent more than 40% of the total collected data or are assumed to be missing either not randomly or completely randomly, then only the collected data will be used for the study’s analysis, and the missing data will be explained as a research limitation in any publications of the study’s findings [Jakobsen et al., 2017].

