**Objective**

**Primary objective:**

To determine the differences in the severity of alcohol dependence, alcohol withdrawal and craving among patients on Lactobacillus sp., placebo and ACT, at 4 timelines (baseline, 8 weeks after starting intervention, 12 weeks after starting intervention, and 24 weeks after starting intervention which is 12 weeks post termination of intervention).

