**Sample size estimation**

A total number of 108 patients are needed, with n=36 per arm inclusive of a possible 20% dropout (total n=90; n=30 per arm, without dropout). The sample size was calculated for a parallel group study design involving three arms and was based on power design analysis. This is a higher number required for the primary outcome of AD, and types of interventions as described below. All these calculations were based on the need for a continuous response variable from independent control and experimental subjects, with a ratio of control to subject fixed at 1:1, power of 0.80 and Type-I error probability associated with this test of null hypothesis of 0.05.

Based on the use of ACT for reducing alcohol craving in patients with alcohol use disorder (AUD) and comorbid affective disorder, a sample size of 21 patients per arm is needed, comprising of 26 patients per arm including an additional 20% dropout. The administration of ACT showed decreased OCDS score with a standard deviation of 4.6 within group was observed, accompanied by decreased score of 4.0 between ACT and control groups[42].

Based on the use of probiotics for reducing alcohol dependence syptom in AD patients, a sample size of 30 patients per arm is needed, comprising of 36 patients per arm including an additional 20% dropout. The administration of probiotics showed decreased HAMD score with a standard deviation of 19.25 within group was observed, accompanied by decreased score of 17.75 between probiotics and control groups[43]. Hence, the estimated number of healthy subjects needed for initial comparison with AD subjects was also at 108 subjects.

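### Four scales are jointly primary and each is tested at 0.05 in the main analysis, with no success rule and no adjustment across them; if any one scale suffices, family-wise error is about 10% to 18.5%

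*Protocol*

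**What the plan says.** The primary objective covers three domains, with no single scale or visit singled out: "To determine the differences in the severity of alcohol dependence, alcohol withdrawal and craving among patients on Lactobacillus sp., placebo and ACT", at four timelines.

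The Data analysis section turns this into four scales under one label: "The mean difference in the primary outcome (CIWA-Ar, PACS, AUDIT, and VAS scores) for the three randomized groups". It then describes two layers of testing.

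- **By visit.** The three groups are compared at each time point, and the differences "will be assessed using one way analysis of variance (ANOVA) followed by false discovery rate adjustment". The family to which the adjustment applies is not defined.
- **Main analysis.** "For the main pool analysis, mixed ANOVA is used to determine the interaction between the groups" and the time points t0 to t3, on the same four scales. No adjustment, ordering or division of alpha is given for this layer.

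The threshold is general: "Statistical significance will be two-tailed and set to p < 0.05". In the Expected results section, the shell of Table 2 gives each scale its own row with a p-value column, and the footnote marks significance at p < 0.05. The Sample size estimation section plans with "power of 0.80 and Type-I error probability associated with this test of null hypothesis of 0.05".

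**The concern.** The plan leaves open what a positive trial is. Read literally, it yields four primary p-values from the main analysis, each compared with 0.05. Nothing prevents a primary efficacy claim from resting on whichever scale crosses the line. Each test may hold its own 5%, but the chance that at least one of the four is falsely positive is larger. The adjustment that the plan does contain belongs to a different set of tests. A false discovery rate procedure would also not, in general, control family-wise error when some of the effects are real.

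At stake is how a result such as an effect on VAS alone could be interpreted: as written, it could be reported as a primary success with no correction for the other three attempts.

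**Working it through.** **Inputs from the protocol.** Four primary scales, three arms, four time points in the mixed ANOVA (t0 to t3), two-tailed 0.05 (Data analysis). 30 evaluable patients per arm, alpha 0.05, power 0.80 (Sample size estimation).

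**Inputs assumed.** Correlation between scales: not given, so varied from 0 to 0.9, equal for all pairs. Correlation between visits within a scale: 0.5. Normal, complete data.

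**1. The plan's own alpha.** For ACT the protocol states SD 4.6, difference 4.0 and 21 per arm. With n = 2(z₀.₉₇₅ + z₀.₈₀)² × SD²/difference²:

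2 × (1.960 + 0.842)² × 4.6²/4.0² = 2 × 7.849 × 1.3225 = 20.8, so 21 per arm.

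The stated 21 reproduces with a single two-sided test at 0.05, so that calculation holds no allowance for several primary scales. The 30 per arm for probiotics exceeds what its inputs give by the same formula (19). That is a separate matter, and the section attributes none of the excess to multiplicity.

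**2. Four independent tests, any one sufficing.**

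1 − (1 − 0.05)⁴ = 1 − 0.8145 = 0.1855, or 18.5%.

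**3. Four correlated tests.** Simulation of 10,000 trials with no true effect, 3 × 30 patients, four visits, four scales, and the group-by-time F test on each scale at 0.05:

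| Between-scale correlation (assumed) | At least one of four significant |
|---|---|
| 0 | 18.1% |
| 0.3 | 17.4% |
| 0.5 | 15.8% |
| 0.7 | 13.5% |
| 0.9 | 9.9% |

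The rejection rate averaged over the single tests was 4.8% to 5.0%, so each test is valid on its own. A separate run of 3,000 trials gave 19.6%, 16.8%, 14.9% and 13.5% at correlations 0, 0.3, 0.5 and 0.7, which agrees within simulation error.

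**4. If all four had to be significant.** In the 10,000-trial simulation all four were significant together in 0% to 1.6% of null trials. Under that rule there is no inflation.

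**5. After adjustment.** Bonferroni at 0.05/4 = 0.0125 gives 1 − (1 − 0.0125)⁴ = 4.9% if independent, and at most 5% under any dependence. Holm has the same bound and rejects at least as often.

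**6. Power at 0.0125 with 30 per arm.** Power ≈ Φ(difference/(SD√(2/30)) − z₀.₉₉₃₇₅), with √(2/30) = 0.2582 and z = 2.498.

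- ACT inputs: 4.0/(4.6 × 0.2582) = 3.368, and Φ(0.870) = 80.8% (92.0% at 0.05).
- Probiotic inputs: 17.75/(19.25 × 0.2582) = 3.571, and Φ(1.073) = 85.8% (94.6% at 0.05).

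These inputs are for OCDS and HAMD, neither of which is a primary scale, and for two-group comparisons. They are a guide only and do not give the power of the interaction tests.

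**The case against.** **The 0.05 is a per-test rate.** The sample size section speaks of the error probability of a test, and each interaction test does hold about 5%. No section promises family-wise control. This stands: a reader might infer that a stated 5% trial-wide guarantee is broken, but the protocol makes no such guarantee. What remains is that the family-wise error is uncontrolled under the any-one-scale reading.

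**All four scales might be required.** That would remove the inflation. The protocol nowhere says so, and the rule would fit poorly. The Operational definition section has withdrawal symptoms improving within a week, and the treatment plan has them gone at about two weeks, while the mixed ANOVA starts at week 2. Little CIWA-Ar signal may be left to test.

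**The statistical analysis plan may supply the rule.** It may, and it is not shown. But the protocol itself fixes four primary scales, the main test and the 0.05 threshold, and what counts as primary success belongs with that choice.

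**Stronger readings that the document does not support.**

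- A reader might count the group main effects as further primary tests and arrive at a higher error. The protocol says only that main effects are shown as estimated marginal means with standard errors; the stated purpose of the mixed ANOVA is the interaction.
- A reader might say that the plan cannot show when the arms differ. The by-visit ANOVAs partly address this, and pairwise contrasts are commonly specified in the statistical analysis plan.
- A reader might add that the sample size rests on two-group comparisons while the main test is a three-group interaction. That is a question about sizing and has no bearing on the error rates here.

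**Conclusion.** The concern holds in a conditional form. With four joint primary scales, no success rule and no adjustment on the main analysis, the chance of at least one false-positive primary result is 18.5% under independence and falls to about 10% at a between-scale correlation of 0.9. That is roughly two to four times 0.05 (9.9/5 = 2.0; 18.5/5 = 3.7).

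The size rests on two assumptions: that significance on any one scale would be called success, and the assumed correlations. PACS and VAS both measure craving, so some positive correlation is likely and 18.5% is best read as the upper end. No correlation examined brings the figure near 5%.

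**What to change.** State in the Data analysis section that the four group-by-time interaction tests (CIWA-Ar, PACS, AUDIT, VAS) form one family, tested with Holm at overall two-sided 0.05 (ordered thresholds 0.0125, 0.0167, 0.025, 0.05) or with Bonferroni at 0.0125 each. Add that a primary claim may be made only for scales significant after adjustment. This keeps all three domains of the primary objective, and it should be settled before the allocation is released for analysis.

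Alternatively, the sponsor may name one of the four scales as the single primary outcome and make the others secondary. That keeps 0.05 for one test but narrows the primary objective, so the objective would have to be reworded as well.

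Cost: wording. A single scale with p between 0.0125 and 0.05 may no longer count as a primary success, and power per scale falls somewhat. On the protocol's own pairwise inputs, 30 per arm still gives about 81% (ACT) and 86% (probiotic) at 0.0125, subject to the caveat that those inputs do not come from the primary scales.

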**Research Question(s)**

1. Does probiotic or ACT result in significant improvement in biological markers, and reduce the degree of AD symptoms severity among patients diagnosed with alcohol dependence after 8 weeks of intervention?

2. Does probiotic or ACT result in significant improvement in rate of alcohol repetition and alcohol withdrawal symptoms and degree of craving?

3. Whether ACT treatment or probiotics can cause EEG changes in alcohol dependent patients?

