**Secondary objectives:**

(1) To determine the differences in the serum levels of pro-inflammatory cytokines among patients on Lactobacillus sp., placebo and ACT, at 4 timelines (baseline, 8 weeks after starting intervention, 12 weeks after starting intervention, and 24 weeks after starting intervention which is 12 weeks post termination of intervention).

(2) To assess the differences in severity of depression and anxiety symptoms among patients on Lactobacillus sp., placebo and ACT via use of questionnaire, at 4 timelines (baseline, 8 weeks after starting intervention, 12 weeks after starting intervention, and 24 weeks after starting intervention which is 12 weeks post termination of intervention).

(3) To investigate the changes of EEG characteristics in patients with AD after the above related treatments, at 3 timelines (baseline, 2 weeks after starting intervention, 8 weeks after starting intervention).

(4) To assess the differences in gut microbiota profiles of patients on Lactobacillus sp., placebo and ACT via the use of fecal samples, at 3 timelines (baseline, 2 weeks after starting intervention, and 8 weeks after starting intervention).

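### The group-by-time model fixed over t0 to t3 does not fit the three EEG visits, and no planned test adjusts week-8 EEG for the pre-intervention recording

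*Protocol*

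**What the plan says.** Research question 3 is causal: "Whether ACT treatment or probiotics can cause EEG changes in alcohol dependent patients". Secondary objective 3 reads "To investigate the changes of EEG characteristics in patients with AD after the above related treatments, at 3 timelines", and gives the visits as "baseline, 2 weeks after starting intervention, 8 weeks after starting intervention". It names no comparison of arms, whereas its neighbour, objective 4, does: "To assess the differences in gut microbiota profiles of patients on Lactobacillus sp., placebo and ACT".

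The Data analysis section sets out two tests for the primary outcomes. The three groups at each time point "will be assessed using one way analysis of variance (ANOVA) followed by false discovery rate adjustment". For the main analysis, "mixed ANOVA is used to determine the interaction between the groups (ACT, probiotic, and placebo groups) and time points (t0, t1, t2, and t3"). In the list of time points, pre-intervention stands first without a label. The label t0 is attached to the next entry, "2 weeks at completion of conventional treatment [t0"], and t1, t2 and t3 follow at 8, 12 and 24 weeks. The analysis of the secondary outcomes, "pro-inflammatory cytokines, EEG characteristics, and fecal microbiota) will be conducted similarly" to that of the primary outcomes. No EEG-specific visit list and no baseline covariate is given there.

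**The concern.** EEG has no recording at week 12 or week 24, so t2 and t3 are empty for it. If t0 is week 2, as the label is placed, the EEG model is left with weeks 2 and 8. Intervention has by then been running for two weeks, so week 2 is not a baseline. The group-by-time interaction over those two visits asks only whether the arms move apart between week 2 and week 8. Any treatment effect already present at week 2 is subtracted out.

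At stake is the answer to research question 3. A treatment that changes EEG early and keeps it changed could give a null result in the analysis that the Protocol calls its main one, while the week-8 comparison shows a difference. Separately, the pre-intervention EEG is collected but is not used to sharpen the week-8 comparison.

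**Working it through.** **Inputs from the Protocol.** 30 evaluable patients per arm (Sample size estimation); two-sided 0.05 (Data analysis); EEG at weeks 0, 2 and 8 (secondary objective 3). There is no EEG effect size, SD or correlation, so there is no EEG figure of the plan to reproduce.

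**Assumptions.** Unit SD at each visit. One arm differs from the other two by 0.74 SD at week 8, which is about the smallest pairwise difference that 30 per arm detects with 80% power (0.736 SD). A fraction f of that effect is present at week 2. Correlation between visits is r = 0.3, 0.5 or 0.7, equal for all pairs unless stated. Each test is at 5%, without the false discovery rate step and for a single EEG measure.

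**Formula.** For a three-arm F test with one arm shifted by δ and residual variance σ², the noncentrality is λ = n × (2/3) × δ²/σ² = 20 δ²/σ².

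**1. Planned week-8 one-way ANOVA.** δ = 0.74, σ² = 1, so λ = 20 × 0.5476 = 10.95. Power is 0.84.

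**2. Week-8 ANCOVA on pre-intervention EEG.** σ² = 1 − r² = 0.91, 0.75, 0.51, so λ = 12.04, 14.60, 21.47. Power is 0.87, 0.93, 0.99, whatever f is.

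**3. Interaction, literal reading (weeks 2 and 8).** This equals a one-way ANOVA on the week 8 minus week 2 difference: δ = 0.74(1 − f), σ² = 2(1 − r).

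| r | f = 0 | f = 0.25 | f = 0.5 | f = 1 |
|---|---|---|---|---|
| 0.3 | 0.69 | 0.44 | 0.21 | 0.05 |
| 0.5 | 0.84 | 0.58 | 0.29 | 0.05 |
| 0.7 | 0.97 | 0.81 | 0.45 | 0.05 |

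The last column follows from δ = 0 and needs no EEG assumption.

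**4. Interaction if t0 means baseline (weeks 0 and 8).** δ = 0.74, σ² = 2(1 − r). Power is 0.69, 0.84, 0.97 for every f. Week 2 is unused.

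**5. Interaction adapted to weeks 0, 2 and 8.** There are 4 and 174 degrees of freedom, and λ = 20 S/(1 − r), where S is the sum of squared deviations of (0, 0.74f, 0.74) from their mean. At f = 0 or 1, S = (2/3) × 0.5476 and λ = 10.43, 14.60, 24.34. At f = 0.5, S = 0.5 × 0.5476 and λ = 7.82, 10.95, 18.25.

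| r | f = 0 or 1 | f = 0.25 or 0.75 | f = 0.5 |
|---|---|---|---|
| 0.3 | 0.723 | 0.620 | 0.580 |
| 0.5 | 0.872 | 0.785 | 0.747 |
| 0.7 | 0.985 | 0.957 | 0.940 |

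Simulation gives the same to about a percentage point: 58–73%, 74–88%, 94–98%.

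**6. Group main effect of the literal week 2 and 8 model.** δ = 0.74(1 + f)/2, σ² = (1 + r)/2. At f = 1 the power is 0.96, 0.93, 0.90.

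**7. When ANCOVA is not the better test.** The week 2-to-8 interaction has more power than ANCOVA when, apart from one degree of freedom, (1 − f)²/[2(1 − r(2,8))] exceeds 1/(1 − r(0,8)²). With equal correlations this never happens, because 1 − r² < 2(1 − r). With f = 0 it happens once r(2,8) passes 1 − (1 − r(0,8)²)/2, which is 0.545, 0.625, 0.745 at r(0,8) = 0.3, 0.5, 0.7. With f = 0.5 the thresholds rise to 0.89, 0.91, 0.94. Examples at f = 0 and r(2,8) = 0.7: 0.97 against 0.93 at r(0,8) = 0.5, and 0.97 against 0.87 at r(0,8) = 0.3.

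**The case against.** The strongest reply is that the t0-to-t3 model is written for the primary outcomes, and EEG is only to follow it by analogy. Since two of the four visits do not exist for EEG, the model must be adapted anyway, and objective 3 supplies the obvious visits. On that reading the pre-intervention EEG stays in the model and the 5% figure becomes 72–98%. This stands in large part. It removes the serious loss, but it depends on the analyst choosing that reading, because the Data analysis section does not state it.

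The label t0 may also mean baseline. The primary objective has four timelines starting at baseline, and the shell of Table 2 starts at pre-intervention. This stands as a real ambiguity. It does not repair the fit, because the EEG model then loses week 2.

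Even on the literal reading an early persistent effect would not go unseen. The group main effect, which is also to be reported, has 90–96% power there, and the week-8 ANOVA has 84%. This stands. What is missing is a statement of which result answers research question 3.

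A reader might infer from objective 3 that no comparison of arms on EEG is planned. The text does not support that: the Data analysis section carries the three-group comparison over to EEG, so the gap is one of wording. Nor do the documents support reading the tests as biased by the benzodiazepine taper, since routine treatment is common to all arms.

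Finally, the choice of a covariate for a secondary outcome is often left to the SAP, which is not at hand. That is fair, and it is why the absence of ANCOVA counts here as an available improvement and not as an error.

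**Conclusion.** The point holds as a minor one. The visit set fixed for the main model matches the EEG schedule on neither reading of t0, and no planned test adjusts for pre-intervention EEG.

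The size depends on the reading. Taken literally, the interaction has 21–45% power when half the effect is present at week 2, and 5% when all of it is. Adapted to weeks 0, 2 and 8, it keeps roughly 58–98% across the correlations considered. It would be tempting to conclude that the plan discards baseline EEG and cannot detect early effects. The documents do not support that as a general statement, because it is true only of the interaction and only on the literal reading.

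The gain from ANCOVA over the planned week-8 ANOVA is modest at r = 0.3 (87% against 84%) and useful at 0.5 and 0.7 (93% and 99%). In sample-size terms, 30/(1 − r²) makes it worth 33, 40 or 59 patients per arm instead of 30. ANCOVA is not uniformly better than the week 2-to-8 interaction, as step 7 shows, and the exceptions do not require pre-intervention EEG to be a weak predictor.

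All power figures rest on an assumed effect of 0.74 SD in one arm and assumed correlations. Only the 5% figure follows from the design alone.

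**What to change.** Base the answer to research question 3 on the week-8 difference between arms adjusted for pre-intervention EEG (ANCOVA), and say so. If the mixed ANOVA is kept for EEG, list its visits as pre-intervention, week 2 and week 8, and state which visit t0 denotes. As a clarification, word objective 3 as a difference among the three arms, in line with the other objectives, and note that within-arm change over time is descriptive.

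The cost is a few lines of text and one model on data already being collected, with no extra visits or patients. The downside is some loss of power compared with the week 2-to-8 interaction if little effect has appeared by week 2 and week 2 correlates clearly more strongly with week 8 than the pre-intervention recording does (for example 93% instead of 97%).

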| IL-6 |  |  |  |  |  |  |  |  |  |  |  |
| TNF-α |  |  |  |  |  |  |  |  |  |  |  |
| Fecal microbiota level |  |  |  |  |  |  |  |  |  |  |  |

* statistical significance at p < 0.05, Pro = probiotics group, ACT = acceptance and commitment group and Con = control group

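### EEG and stool are collected only up to week 8, but the analysis carried over to them and the microbiota row of Table 2 run to weeks 12 and 24

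*Protocol*

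**What the plan says.** **Collection.** Under Secondary objectives, item (3) schedules EEG "at 3 timelines (baseline, 2 weeks after starting intervention, 8 weeks after starting intervention", and item (4) gives stool the same three visits. Item (1), on cytokines, and item (2), on depression and anxiety, use a different set: "at 4 timelines (baseline, 8 weeks after starting intervention, 12 weeks after starting intervention, and 24 weeks after starting intervention which is" 12 weeks after the intervention ends.

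**Analysis.** For the primary scales, the Data analysis section lists an unlabelled pre-intervention point, then a two-week point labelled t0, then t1, t2 and t3 at weeks 8, 12 and 24. The mixed ANOVA tests the group-by-time interaction over "time points (t0, t1, t2, and t3". For the secondary outcomes it says only that the analysis of these ("severity of anxiety and depressive symptoms, pro-inflammatory cytokines, EEG characteristics, and fecal microbiota) will be conducted similarly to the primary" outcomes) follows suit. No separate time points are given.

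**Reporting.** Table 2, under Expected result(s), has three time columns: pre-intervention, 12 weeks and 24 weeks. One of its rows is "Fecal microbiota level".

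**The concern.** Three parts of the protocol disagree about when EEG and stool are observed. The objectives stop at week 8, the inherited analysis continues to week 24, and the table shell reports microbiota at two visits when no stool is taken while giving no place to two visits when it is.

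A mixed ANOVA with time as a within-subject factor needs a value at every level for each subject. If two of the four levels are never scheduled for an outcome, the specified interaction test cannot be run on it. The analyst would then have to choose the time points, possibly after seeing the data. If t0 is week 2, the pre-treatment EEG and stool values, which are the natural reference, would also stay outside the test.

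**Working it through.** The protocol gives no figure to reproduce here. The check compares sets of weeks, with baseline written as week 0.

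**Inputs**
- EEG and stool collected at {0, 2, 8}: Secondary objectives (3) and (4).
- Cytokines, HAMD and HAMA collected at {0, 8, 12, 24}: Secondary objectives (1) and (2).
- Mixed ANOVA levels t0 to t3: Data analysis. As labelled, t0 is week 2, giving {2, 8, 12, 24}. If t0 was meant as the pre-intervention visit, the levels are {0, 8, 12, 24}.
- Table 2 columns: {0, 12, 24}, for three arms.
- Planned size: 36 per arm, 3 × 36 = 108 in total (Sample size estimation).

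**Levels available = analysed weeks ∩ collected weeks**

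| Outcome | t0 = week 2 | t0 = baseline |
| --- | --- | --- |
| EEG, stool | {2, 8}: 2 of 4 | {0, 8}: 2 of 4 |
| Cytokines, HAMD, HAMA | {8, 12, 24}: 3 of 4 | {0, 8, 12, 24}: 4 of 4 |

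For EEG and stool, weeks 12 and 24 are absent on both readings, so 2/4 = 50% of the levels are absent by design. With perfect attendance, 0 of 36 subjects per arm (0 of 108) have all four levels.

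For cytokines, HAMD and HAMA the result turns on t0. If t0 is week 2, one level of four is absent and nobody is complete. If t0 is baseline, all four are present and up to 36 per arm are complete.

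**Visit-by-visit one-way ANOVAs.** The Data analysis section lists five points, {0, 2, 8, 12, 24}. EEG and stool have 3 of the 5.

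**Table 2, microbiota row.** {0, 12, 24} ∩ {0, 2, 8} = {0}. One column × 3 arms = 3 cells that can be filled, out of 3 × 3 = 9. The other 2 × 3 = 6 cannot. Stool from weeks 2 and 8 has no column.

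**With the time factor matched to collection.** EEG and stool have 3 of 3 levels, with up to 36 complete subjects per arm and 9 of 9 microbiota cells fillable.

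**The case against.** The best defence is that saying the secondary outcomes are handled similarly describes a method and does not fix visits. The t0 to t3 set is attached to the primary scales, and the objectives already give each secondary outcome its own visits, so the natural course is the same ANOVA over those visits. This is fair as a guess at intent, and it is close to the fix below. But the Data analysis section does not say it, and Table 2 points the other way by putting microbiota at weeks 12 and 24.

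Table 2 is only an empty shell and visibly unfinished: it has no week-8 column for any outcome, and the neighbouring Table 1 carries a column for a treatment that is not in this trial. That makes the impossible cells a drafting slip, but they still need correcting. The absence of an EEG row is not an error, because a full set of tables can be left to a statistical analysis plan.

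Two stronger readings are tempting, and the protocol does not support either.
- A reader might infer that no secondary outcome can be analysed as planned. For cytokines, HAMD and HAMA this requires t0 to be week 2. That is the literal label, and items (3) and (4) do treat week 2 as distinct from baseline. Yet the four labels t0 to t3, the four visits in the objectives and the four assessments counted under Honorarium and incentives leave open that t0 was meant as baseline. The primary scales have the same schedule and the same ambiguity, so it is not a separate defect of these outcomes.
- A reader might infer that the unscheduled visits would trigger the missing-data rule, with its band of "more than 5% but less than 40% of the total collected". Those percentages refer to the study's total data rather than to one outcome, and nothing there counts a visit that was never planned as missing.

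**Conclusion.** The concern holds for EEG and stool on either reading of t0: 2 of 4 levels, no subject complete for the t0 to t3 mixed ANOVA, and 6 of 9 microbiota cells in Table 2 that cannot be filled. This is a contradiction within the protocol, between Secondary objectives, Data analysis and Table 2, and not a detail left for a later plan. For cytokines, HAMD and HAMA there is a gap only if t0 is week 2, and defining t0 as the pre-intervention baseline removes it.

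The conclusion assumes that the objectives state the true collection schedule and that the t1 to t3 weeks are counted from the start of intervention, as the objectives count them. The study flowchart is not visible and may list visits, but it could not by itself reconcile the three written sections. The matter affects secondary outcomes only and can be corrected in wording, so it should be settled before analysis but does not threaten the primary comparison.

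**What to change.** In Data analysis, state the time factor by outcome:
- EEG and fecal microbiota: baseline, week 2 and week 8.
- Cytokines, HAMD and HAMA: baseline and weeks 8, 12 and 24.
- Define t0 explicitly as the pre-intervention baseline. This also settles the shared ambiguity for these outcomes and the primary scales.

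In Table 2, report microbiota at baseline, week 2 and week 8, and EEG likewise if it is tabulated. Which of these visits carries the main EEG or microbiota contrast is the sponsor's choice.

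The cost is analysis wording and a table shell, with no added visit, sample or patient. The downside is that the protocol must acknowledge that EEG and microbiota say nothing about effects after week 8.
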